### Surgical treatment

The fractures will be fixed within 8 days of the initial trauma in both groups using standard AO (Arbeitsgemeinschaft für Osteosynthesefragen) [22] principles. Antibiotic prophylaxis will be given perioperatively. Open reduction and internal fixation (ORIF) of fibula fractures will be treated either with a 1/3 tubular plate with or without lag screws or in high fibula fractures with syndesmosis fixation only. Additional fractures of medial and/or posterior malleolus will be treated according to standard principles before stabilizing the syndesmosis. The distal tibiofibular joint will be reduced without direct visualization of the syndesmosis and held at its anatomical position by a reduction clamp. The ankle joint will be positioned at an angle of 90° between the tibial shaft and the foot during syndesmosis fixation in accordance with the randomization (cortical screw or TightRope®).

For the static syndesmotic screw fixation, a 2.5-mm hole will be drilled under fluoroscopic guidance, approximately 2 cm above and parallel to the distal tibial joint line from lateral to medial. If plating of the fibular fracture is necessary, the hole will be drilled through an empty screw hole. Three cortices will be drilled through and a 3.5-mm screw will be tightened.

For the dynamic fixation of the syndesmosis by means of TightRope®, a 3.5-mm hole will be drilled under fluoroscopic guidance, approximately 2 cm above and parallel to the distal tibial joint line (through a hole of the plate if present) from lateral to medial. A guide needle will be inserted from lateral to medial through the drill hole to position the oblong button over the medial tibial cortex and confirmed by X-ray. Afterwards, the assembly will be tensioned by pulling the free ends of the FiberWire on the lateral side. These will be hand-tied with a surgical knot and the round button will be firmly applied on the lateral cortex of the fibula (or onto the plate if present). After achieving an adequate syndesmotic fixation by either technique, the reduction clamp will be removed and the stability controlled under fluoroscopy.

After syndesmosis fixation, intraoperative CT/3D imaging with ISO C 3D or CIOS Spin (Siemens Healthineers GmbH, Deutschland) will be performed to evaluate syndesmosis reduction.

The postoperative treatment protocol is similar in both groups. The ankle will be immobilized in a below-the-knee cast with the ankle joint at 90° for 6 weeks with partial weight-bearing. Between the 6th and 8th week, only the static syndesmosis screw will be removed in a standardized outpatient surgery. The dynamic fixation of the syndesmosis by means of TightRope® needs no removal postoperatively. Afterwards, weight-bearing can be gradually increased with approximately 20 kg per week until full weight-bearing is achieved.

### Follow-up

Subsequent to surgery, all patients will receive similar follow-up procedures. Follow-up at our trauma center is standardized, based on a well-established protocol, and all procedures and diagnostics are based solely on medical indications. First radiological and clinical evaluation of the surgical treatment will be performed on day 2 after surgery. Discharge from hospital will be realized as soon as general health conditions (soft tissue conditions, patient mobility and pain level) allow it. Afterwards, patients will receive physiotherapy and manual lymphatic drainage. Further clinical and radiographic evaluations are planned for 6 weeks and 3, 6, and 12 months after surgery following our standardized procedure for fracture patients treated in our hospital (Table 1). There are no additional follow-up appointments or X-ray examinations necessary for the study. Merely the gait analysis and MRI control of the syndesmosis will be performed 6 months postoperatively during the regular follow-up appointment.

**Table 1 Tab1:**
[figure not shown]
Overview of clinical and radiologic follow-up. *CT* computed tomography, *MRI* magnetic resonance imaging, *SF-12* 12-item Short Form Health Survey, *VAS pain* visual analog scale for pain

MRI images will be assessed by a senior radiologist for degenerative changes of the tibiotalar joint and the syndesmosis structure (unaffected, hyperintense signal alteration on T2, partial tear, complete tear), widening, and calcification. By using questionnaires preoperatively and postoperatively after 6 weeks and 3, 6, and 12 months during the appointments, patients can provide information on pain, mobility of foot and ankle, and quality of life (SF-12) [19] during the course of treatment. General patient data, including age, profession, body mass index (BMI), risk factors, medication, concomitant diseases, previous surgeries, and details of the accident, will be documented preoperatively.

At 25 weeks postoperatively, patients also receive a gait analysis and MRI is performed to assess motion anomalies and the healing process of the syndesmosis.

The planned study will run over 2 years. Patients will be admitted over a period of 1 year. Each patient will be treated and followed-up over a 12-month period.

All data will be stored and monitored using pseudonyms. The data of all patients will be analyzed statistically and compared at the end of the 2 years (Table 1).

Furthermore, all data of the participating patients will be carefully assessed, and all adverse events and complications of the treatment will be reported at the end of this trial. The harms will be categorized according to their degree of severity in either serious or non-serious.

### Criteria that lead to termination of study

Every participant is able to withdraw their consent to participate in the trial at any time without giving reasons. Thereby, the recorded study data may be destroyed immediately upon request or, with the consent of the participant, can still be included in the evaluation.

If initial data indicates either impossible realization due to technical difficulties or an increased risk for the participants that is potentially harmful, the study will be terminated immediately.

### Sample size calculation and statistical analyses

Formal sample size determination is not possible as potential effects are not yet known. Data from previous studies were utilized to determine the necessary sample size [23–25]. We plan a sample size of 25 patients, who will be treated with the cortical screw fixation and 25 patients, who will be treated with the dynamic TightRope® system within 2 years. The patients will be randomized to the two different treatment options. The randomization will be independent of the surgeon and the doctor who will do the examinations and the questionnaires.

The Shapiro-Wilk test will be used to check if our population is normally distributed. Standard unpaired Student’s *t* test to detect significant changes between the two groups will be conducted, if they are normally distributed. In contrast, possible differences for continuous data and scores between groups will be evaluated with the Wilcoxon *U* test, if no normal distribution exists.

The empirical distribution of continuous data and scores will be reported and calculated with means, standard deviation (SD), median, minimum, and maximum values and with absolute and relative frequencies for categoric data as well as unpaired *t*-test *p* values to depict a significant difference between the different groups. All descriptive analyses will be calculated for demographic data and for the dependent variables derived from the functional assessment, gait analyses results, and questionnaires of both groups.

An independent senior statistician of the Institute of Medical Biometry and Informatics of our university will perform the analysis. The intention-to-treat population will be used.

The analysis and illustrations will be carried out by use of SPSS version 25.0 for 135 Windows (IBM Corp., Armonk, New York, USA) and GraphPad Prism version 6.00 for Windows (GraphPad Software, San Diego, California, USA). For the representation of statistical relationships, the Pearson correlation coefficient will be used. The final details of the statistical analysis will be established in a statistical analysis plan, which will be completed before the closing of the database (before the end of data collection). A *p* value of ≤ .05 will be used to indicate statistical significance. Only a complete follow-up examination will be considered in the statistical analyses.

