The most popular treatment option of the unstable distal tibiofibular joint is a static 3.5-mm screw fixation (FA DePuy Synthes, USA) with one or multiple screws through three or four cortices. Disadvantages of the syndesmosis screws are partial weight-bearing for at least 6 weeks, neglect of the dynamic property of the syndesmosis, and an increased risk of chronic instability as well as the potential of late diastasis due to loosening, screw breakage, or screw removal. Furthermore, syndesmosis malreduction is reported to occur in up to 50% with syndesmotic screw fixation [8, 9]. Six to 8 weeks after the initial treatment, a mandatory implant removal is required to begin weight-bearing at our trauma center. In contrast, some authors prefer to retain the syndesmotic screw in place until she breaks. Whether or not the syndesmotic screw should be removed prior to weight-bearing is still discussed [10].

In contrast to screw fixation, the flexible, dynamic TightRope® (Arthrex, Naples, FL, USA) suture button device was developed for physiological stabilization of the distal tibia and fibula. The use of this dynamic suture button device has increased rapidly over the last years. Theoretically, this suture button device allows physiological motion of the syndesmosis without need for implant removal, which may reduce the risk of recurrent syndesmotic diastasis as described after syndesmosis screw removal [11, 12].

Biomechanical investigations have demonstrated that the strength of TightRope® device is comparable to a tricortical 3.5-mm syndesmotic screw. Several recent studies assessed syndesmosis stabilization with the suture button device and comparative studies reported equivalent or better functional results in comparison to the syndesmotic screw [3, 13–16].

Instrumented gait analysis is a well-established procedure at our trauma center, which allows objective quantification of gait deviations in the context of conservative and surgical treatment in the lower extremity. For assessment, the patient is equipped with skin-based markers and asked to walk repeatedly along a 5-10-m-long walkway at self-selected speed for monitoring joint motion via optical motion tracking. Floor mounted force plates allow for determining ground reaction forces when walking across them. This so-called “standard clinical instrumented 3D gait analysis” is a modern in vivo analysis, which allows for analyzing joint motion and joint kinetics of the major lower limb joints [17, 18].

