### Randomization

Patients will be randomly assigned to one of two groups (intervention or control) using a computer-generated random block assignment in a 1:1 ratio using nQuery Advisor v7.0 software (Statsols, Cork, Ireland). This method helps in maintaining the balance of treatment assignment while reducing the potential for selection bias. Patients, researchers performing the follow-up examination, and the trial statistician will be blinded to the group allocation. If the treatment of syndesmosis rupture is not accomplished after randomization due to an intraoperatively observed missing acute syndesmosis rupture with no need of stabilization, the patient will be excluded from final analysis. At the date of screw removal 6 to 8 weeks after the operation, a blinding of the patients will no longer be possible.

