## Discussion

The objective of this prospective randomized controlled single-center study is the comparison of the gait analysis, clinical and radiographic outcome after stabilization of an acute syndesmosis rupture with either a static implant (a 3.5-mm metallic screw through three cortices) or a dynamic device (TightRope®).

The study aims to investigate the clinical, biomechanical, and radiographic outcome of TightRope® as a dynamic stabilization device compared to the gold standard, the static screw device after acute syndesmosis ruptures of the ankle.

A lot of studies investigated the equality of both treatment options with numerous advantages of the suture button device over the screw fixation [28]. Zhang et al. described in their review that both devices had similar functional outcomes and postoperative complication rates. Furthermore, TightRope® device leads to a better range of motion and earlier return to work, compared to the screw fixation. Besides, TightRope® fixation groups had lower rates of implant removal, implant failure, and malreduction.

Actually, there is no human study with focus on objective biomechanical outcome measurements by using a gait analysis. Former biomechanical studies have demonstrated the advantages of the dynamic fixation of the syndesmosis only in animals or models [13, 29–31].

In the current study, we use the OMAS score, as it is the only validated assessment tool for ankle fractures. It detects clinical differences between treatment groups with a higher sensitivity and specificity as other scores [32].

In our study, weight-bearing is allowed after 6 weeks in both groups and only after screw removal in the intervention group, although many studies have proposed earlier weight-bearing with the dynamic fixation on the one hand [14, 33]. On the other hand, the static screw fixation prohibits early weight-bearing especially because of a high risk of screw breakage. These studies show that early weight-bearing is associated with a shorter recovery time as well as a quicker return to main activities.

Furthermore, the need and timing for postoperative routine syndesmotic screw removal are still subject to controversial discussions. In accordance with AO principles, elective routine screw removal prior to the beginning of full weight-bearing is carried out in our trauma center between the 6th and 8th week after surgery.

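### Minor improvement: the t test is named in its equal-variance Student form with only a normality check; Welch's form would hold the .05 level if arm sizes and spread both turn out unequal, at negligible cost

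*Protocol article*

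**What the plan says.** All of the analysis rules are in the protocol article, section Sample size calculation and statistical analyses.

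- The Shapiro-Wilk "test will be used to check if our population is normally distributed".
- If normality holds, the standard unpaired Student's t form is used: this "test to detect significant changes between the two groups will be conducted, if they are normally distributed". Otherwise continuous data and scores go to the Wilcoxon U test. Unpaired t-test p values are also to accompany the descriptive tables.
- Significance: a p "value of ≤ .05 will be used to indicate statistical significance". Whether this is one- or two-sided is not stated.
- Size: "We plan a sample size of 25 patients, who will be treated with the cortical screw fixation and 25 patients" with TightRope. No SD, effect size or power is given. The Randomization section allocates "using a computer-generated random block assignment in a 1:1 ratio".
- Two rules can reduce an arm after randomisation. If no acute rupture needing stabilisation is found at surgery, "the patient will be excluded from final analysis" (Randomization). The statistics section also restricts the analyses to patients with complete follow-up.
- Final statistical details are deferred to an analysis plan that is not shown.

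**The concern.** The Student form pools the two sample variances. It holds its level if the population variances are equal, and very nearly so if the arms are equal in size. The article makes use of the test depend on normality alone, so the other assumption is neither checked nor avoided.

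If both spread and arm size differ, the pooled standard error is biased, and the direction depends on which arm is which. When the smaller arm is the more variable, the standard error is too small and the test rejects too often. When the larger arm is the more variable, it is too large, and the test rejects too rarely and loses power. Every normally distributed gait parameter and questionnaire score would be affected in the same way.

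**Working it through.** **Inputs from the article:** Student's t test, level .05, 25 and 25 patients. **Assumptions:** two-sided testing, normal data, SD ratio r from 1 to 3 (arm 1 is the more variable, arm 2 has SD 1), and the arm sizes shown. The article gives neither SDs nor loss rates.

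**Step 1. Where the bias comes from.** The true variance of the mean difference is r²/n1 + 1/n2. On average the pooled test uses [((n1−1)r² + (n2−1))/(n1+n2−2)] × (1/n1 + 1/n2). With r = 2:

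- 25/25: pooled (24×4 + 24)/48 × 0.08 = 2.5 × 0.08 = 0.200; true 4/25 + 1/25 = 0.200. No bias.
- 20/25: pooled (19×4 + 24)/43 × 0.09 = 2.326 × 0.09 = 0.209; true 4/20 + 1/25 = 0.240. The standard error is too small by a factor of √(0.209/0.240) = 0.93.
- 25/20: pooled (24×4 + 19)/43 × 0.09 = 2.674 × 0.09 = 0.241; true 4/25 + 1/20 = 0.210. The standard error is too large by a factor of √(0.241/0.210) = 1.07.

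**Step 2. Type I error of the Student test**, by numerical integration over both sample variances. The plan's own case comes first: 25/25 with r = 1 gives 5.00%, which reproduces the stated level.

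| n1 (more variable) / n2 | r = 1.5 | r = 2 |
|---|---|---|
| 25/25 | 5.1% | 5.2% |
| 22/25 | 5.7% | 6.1% |
| 20/25 | 6.1% | 6.9% |
| 18/25 | 6.6% | 7.8% |
| 25/22 | 4.5% | 4.4% |
| 25/20 | 4.2% | 3.8% |

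At 25/25 with r = 3 the figure is about 5.4%. For 24/18, simulation gives 3.9% at r = 1.5 and 3.6% at r = 2 (integration puts the second at 3.5%). At 24/18, with SDs 1.5 and 1 and a true difference of 1.0, power is 67% with Student and 71% with Welch.

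**Step 3. Welch.** Type I error is 4.96 to 5.05% in every case from 25/25 to 15/25, in either direction, with r from 1 to 3.

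**Step 4. Cost of Welch if variances are equal** (true difference 0.8 SD): power goes from 79.15% to 79.09% at 25/25, from 74.11% to 73.93% at 20/25, and from 66.54% to 65.78% at 15/25. That is 0.06, 0.18 and 0.76 points.

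**Step 5. The planned two-step procedure** (Shapiro-Wilk in each arm, then t or U; 20,000 simulated trials at 20/25, r = 2): 7.0% with Student and 5.3% with Welch, so the gain survives the normality gate. The U test used alone gives 6.5% here, and changing the t test does nothing for that branch.

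**Step 6. How likely are the assumed conditions?** With equal independent losses of 10 to 30% per arm (assumed), the mean imbalance is 1.7 to 2.6 patients and the 95th percentile is 4 to 6. If a share p of one arm is shifted by d SD and none of the other is, the SD ratio is √(1 + p(1−p)d²). With p = 0.5 this is √1.25 = 1.12 for d = 1 and √2 = 1.41 for d = 2.

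**The case against.** The strongest case against raising this has four parts.

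**It is a detail for the analysis plan.** Final details are deferred to a document not shown. But the article does not leave the form of the t test open; it names one. A stated choice can be commented on, though the deferral means it can still be changed without difficulty.

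**Nothing in the article says that the spread differs.** A reader might infer it from the Background, where "syndesmosis malreduction is reported to occur in up to 50% with syndesmotic screw fixation", and from the Discussion, where TightRope "fixation groups had lower rates of implant removal, implant failure, and malreduction", picturing a screw arm that mixes good and poor results. The documents do not support that step. These are rates taken from the literature, the first an upper limit, and every patient in this trial has reduction checked by intraoperative 3D imaging. The mechanism is also weak. With half the arm affected, an SD ratio of 1.5 needs d = 2√1.25 = 2.24, which moves the arm mean by 1.12 SD, so the null hypothesis would be false anyway. In a simulation of that mixture at 18/25, Student had 80% power and Welch 76%, partly because Student's level is inflated there. This objection stands: unequal spread is possible but is not shown.

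**Unequal arms are permitted, not implied.** A reader might take the exclusion rules as making the arms unequal. They apply alike to both arms, allocation is 1:1 in blocks, and no loss rate is given. Differential loss through the screw-removal operation is conjecture. Averaged over assumed equal random losses of 10 to 30%, Student's level is 5.0 to 5.4%. This stands too.

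**The consequence is limited.** MRI healing, the first-named primary endpoint, is a classification and uses no t test, and the trial is a pilot. A reader might also conclude that planned confidence intervals are wrong, but the statistics section plans none.

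**Conclusion.** The point holds as a minor, nearly free improvement. The article names the pooled form with no regard to variance. At the planned 25/25 that is sound. Drift in the level requires unequal arms and unequal spread together: about 5.7 to 7% for 20 to 22 against 24 to 25 patients at SD ratio 1.5 to 2 with the smaller arm more variable, and about 3.6 to 4.2% in the reverse case at 25/20 and 24/18. The error can therefore go either way. The SD ratios and arm sizes are assumptions; the documents supply no figure for them and equally none to support equal spread. The documents do not support saying that the .05 level will be missed, that the plan's own rationale predicts unequal spread, or that the change is wholly without cost.

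**What to change.** In the statistics section, and in the analysis plan before the database is closed, replace the standard Student's t test by Welch's unequal-variance t test wherever a t test is used, including the p values that accompany the descriptive tables. Do not add a preliminary test of variances to choose between the two forms.

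The cost is a change of wording, with no extra data, patients or software. The statistical price is the small loss of power in step 4. The U-test branch is unchanged by this.

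### The statistics section assigns the Wilcoxon test to non-normal outcomes, then reports t-test p values for the same variables without that condition and does not say which test prevails

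*Protocol article*

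**What the plan says.** Everything here is in the protocol article, section Sample size calculation and statistical analyses.

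- The second paragraph sets the normality check: "The Shapiro-Wilk test will be used to check if our population is normally distributed". An unpaired Student's t test follows where the data pass ("test to detect significant changes between the two groups will be conducted, if they are normally distributed"). Otherwise, "possible differences for continuous data and scores between groups will be evaluated with the Wilcoxon *U* test, if no normal distribution exists".
- The third paragraph lists the summaries for continuous data and scores (mean, SD, median, minimum, maximum) and frequencies for categorical data, and then adds "as well as unpaired *t*-test *p* values to depict a significant difference between the different groups". No normality condition is attached.
- The sentence after it sets the scope: "All descriptive analyses will be calculated for demographic data and for the dependent variables derived from the functional assessment, gait analyses results, and questionnaires".
- One threshold serves every p value: "A *p* value of ≤ .05 will be used to indicate statistical significance".
- The planned size is 25 patients per arm ("We plan a sample size of 25 patients, who will be treated with the cortical screw fixation and 25 patients", the second 25 being the TightRope arm).
- Remaining detail is deferred: "The final details of the statistical analysis will be established in a statistical analysis plan".

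**The concern.** The two paragraphs give different instructions for the same variables. For a variable that fails the normality check, the second paragraph calls for Wilcoxon. The third paragraph then supplies a t-test p value for it, with the stated purpose of showing significance. The t test is the one that the second paragraph sets aside in that situation.

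The variables concerned are the gait results, a primary outcome under Primary outcome measures, and the questionnaire scores, which are secondary outcomes. If the two p values fall on opposite sides of .05, the reported conclusion depends on which one is cited. The direction matters too. Objectives and hypotheses frames equal outcome as the alternative hypothesis, so a t test that misses a difference which Wilcoxon detects would lean towards the result the investigators expect.

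The scope sentence also names demographic data. If the t-test p values count among the descriptive analyses, baseline characteristics of randomised arms would be tested for significance, although under proper randomisation any difference there is due to chance.

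**Working it through.** The protocol gives no effect size, SD or power, so there is no figure of its own to reproduce. The check has two parts.

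**1. The text, for a variable that fails Shapiro-Wilk**

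| Source | Instruction | Condition |
|---|---|---|
| Second paragraph | Evaluate the group difference with Wilcoxon | Not normal |
| Third paragraph | Report an unpaired t-test p value to show significance | None |
| Threshold sentence | p ≤ .05 | None |

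Taken literally, all three apply at once. That gives two p values for one comparison, both at .05. For a variable that passes, the two paragraphs agree and there is no conflict.

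**2. How often the two p values would disagree**

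Inputs from the protocol: 25 per arm and a threshold of .05. Assumptions: two-sided tests (the protocol does not state sidedness), the distribution shapes, and location shifts of 0, 0.5 and 0.8 SD. A pooled t test and a Mann-Whitney (Wilcoxon) test were run on the same data, with 20,000 simulated trials per scenario.

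Disagreement = P(t only) + P(Wilcoxon only). Either-test rate = P(t significant) + P(Wilcoxon only).

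| Shape | Shift (SD) | t sig. | Wilcoxon sig. | t only | Wilcoxon only | Disagree | Either |
|---|---|---|---|---|---|---|---|
| Lognormal, log-SD 1 | 0 | .041 | .047 | .019 | .024 | .043 | .065 |
| | 0.5 | .554 | .930 | .001 | .378 | .379 | .931 |
| | 0.8 | .833 | .996 | .000 | .164 | .164 | .996 |
| Exponential | 0 | .046 | .047 | .019 | .019 | .038 | .065 |
| | 0.5 | .444 | .677 | .007 | .240 | .247 | .684 |
| | 0.8 | .792 | .939 | .003 | .150 | .152 | .942 |
| t, 3 df | 0 | .043 | .044 | .015 | .016 | .031 | .059 |
| | 0.5 | .502 | .643 | .019 | .160 | .179 | .662 |
| | 0.8 | .831 | .948 | .003 | .121 | .124 | .952 |
| Beta(5, 1.2), left-skewed | 0 | .049 | .047 | .014 | .013 | .027 | .061 |
| | 0.5 | .416 | .487 | .023 | .094 | .117 | .510 |
| | 0.8 | .790 | .841 | .016 | .068 | .084 | .857 |

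Worked lines:
- Lognormal at 0.5 SD: disagreement is .001 + .378 = .379. Wilcoxon-only makes up .378/.379, nearly all of it.
- t with 3 df at 0.5 SD: .019 + .160 = .179, of which Wilcoxon-only is .160/.179 = 89%.
- Lognormal with no difference: the either-test rate is .041 + .024 = .065.

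The two tests applied singly have null rates of .041 to .049 (t) and .044 to .047 (Wilcoxon).

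A second set of 6,000 trials per scenario kept only samples in which Shapiro-Wilk had p ≤ .05 in at least one arm. Applying the check by arm is an assumption.

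| Shape | Disagree at 0.5 SD | Either, no difference |
|---|---|---|
| Lognormal, log-SD 1 | .375 | .068 |
| Exponential | .260 | .063 |
| t, 3 df | .226 | .067 |
| Lognormal, log-SD 0.5 | .179 | .065 |
| Ceiling-limited score | .063 | .058 |

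The low end of the range, 6%, comes from the ceiling-limited score. The beta scenario in the first table is a pure shift that can carry values past the upper bound, so it does not represent a strictly bounded questionnaire.

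**The case against.** The strongest reply is that a rule does exist. The second paragraph is the only text that assigns a test to the evaluation of group differences, and for non-normal data it names Wilcoxon. The t-test clause sits in a paragraph about descriptive reporting and is loosely built: it follows the frequencies for categorical data, to which a t test cannot apply. It may be shorthand for the t test where the normality rule permits it. Final details go to an analysis plan that is to be completed before the database closes, an independent statistician does the analysis, and the Randomization section says the trial statistician is blinded. The trial is a pilot, and MRI healing, the other primary outcome, is a healed or not-healed classification that this point does not touch.

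Much of this stands. A reader might infer that nothing in the plan says which p value decides. The document does not support that, because the normality rule is such a statement and the natural reading is that Wilcoxon decides. A reader might also infer that the choice will be made after both p values are seen. The safeguards just listed count against assuming so.

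The contradiction itself remains. The clause is unconditional and its stated purpose is inferential, so it cannot be treated as purely descriptive, and nothing subordinates it to the rule before it. This is a conflict between two stated instructions, not a detail left out for the analysis plan, and an analysis plan built on this text would inherit both.

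**Conclusion.** The point holds as an internal contradiction: an unconditional t-test p value is set against a rule that assigns Wilcoxon to non-normal data, with no statement that the rule prevails.

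Its main consequence is conflicting verdicts when a true difference exists: about 6% to 38% of trials at a 0.5 SD shift, depending on shape. Under the strongest assumed skew, power is about .55 by t test against .93 by Wilcoxon. For a ceiling-limited score the disagreement is near the bottom of the range.

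A reader might infer a serious inflation of false positives. The figures do not show one: accepting either p value gives about 6% to 7% against 5%, and the plan nowhere says that either may be accepted.

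All sizes rest on assumed distributions and shifts. The protocol gives no data on the shape of ankle range of motion, ankle power or the scores, so the upper end should not be taken as expected. The remark on demographic data depends on reading the t-test p values as part of the descriptive analyses, which the order of the sentences suggests. The contradiction is worth correcting because correction costs almost nothing.

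**What to change.** In the third paragraph of Sample size calculation and statistical analyses, delete the unconditional t-test p values. Add one sentence: each between-arm outcome comparison has a single inferential p value, from the test that the second paragraph assigns to that variable. State that demographic data of the randomised arms are summarised without p values.

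The cost is a change of wording that can be made before the database closes. It removes p values and adds no analysis.

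Naming one test per variable in advance, in place of the Shapiro-Wilk rule, and adding effect estimates with 95% confidence intervals are optional improvements. They go beyond what is needed to remove this contradiction, and the intervals would add output.
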